## Introduction

Primary care is the setting where the majority of people will seek health care. Studies on the ecology of health care show this is the case in the United States, where 52% of patients who consulted a doctor in the past month saw a primary care doctor [1], and also in Hong Kong (84.5% of patients) [2]. Information about the health problems of patients presenting in primary care is therefore crucial to understanding the health of the general community for the planning and allocation of health care resources.

It is important to replicate morbidity surveys from time to time given changing demographic and socioeconomic profiles. In Hong Kong, the last morbidity study was carried out in 2007-2008 [3]. Within the last 10 years (2005-2015), there has been an increase in the proportion of people aged 65 years or older, level of educational attainment, individual and household income, and cross-border immigration from mainland China, while there has been a notable decline in unemployment [4]. These sociodemographic changes are reflected in the health problems and concerns of patients who present to primary care and also in the changing prevalence of various diseases over time [5,6]. Practice-based morbidity surveys conducted at 10-year intervals have been able to capture changes in the prevalence and trends of health problems presenting in primary care as observed in England and Wales (1991-2001) [6] and in Hong Kong (1994-2007) [3,7].

Superimposed on this background is the expectation that chronic disease and psychological problems will continue to be a major burden of illness globally and in Hong Kong as we move deeper into the 21st century [8]. There is increasing pressure for primary care to shoulder the care for the majority of these patients given the volume of patients and the demonstrated effectiveness and cost-effectiveness of family doctor–led primary care [9]. Local Hong Kong evidence shows that chronic disease makes up an increasing proportion of problems seen by primary care doctors, with the bulk of patients seen in public outpatient clinics [10].

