Since the last morbidity study in Hong Kong in 2007-2008 [3], the Hong Kong Government has implemented some primary care initiatives in response to the increasing burden on public general outpatient clinics (GOPC) such as the GOPC Public-Private Partnership, Elderly Health Care Voucher Scheme, and the Vaccination Subsidy Scheme. These aim to encourage patients to seek care in the private sector, particularly for care of chronic diseases. Tracking morbidity and management trends would provide an indication of the impact of these initiatives on the prevalence of chronic disease and its care in both public and private primary care sectors.

Apart from the morbidity pattern, specific information on the management pattern such as prescription, investigation, referral to specialists, health promotion, and disease prevention is important for assuring the quality of primary care services and for identifying support services needed. In 2014-2015, there were an estimated 6 million primary care encounters in the public sector alone [11], which extrapolates to about 30 million primary care encounters in the combined public (20% of total encounters) and private sectors across Hong Kong [12]. The most recent morbidity study found that the Hong Kong referral rate to specialists was 2.5% in 2007-2008 [3], which means that even a small increase of 1% in referral rate would produce a huge relative increase of 40%, translating to an additional 300,000 specialist referrals. Changes in consultation trends in primary care do occur [13], with substantial potential impact on health care service needs and expenditures, and must be monitored.

With an aging population, increasing prevalence of chronic disease, and the implementation of primary care initiatives to shift some of the burden of chronic disease care from the public to the private sector, a primary care morbidity study is timely and important to document and evaluate the impact of these changes.

This study aims to determine the changes in morbidity and management patterns in Hong Kong primary care compared with the patterns identified in the morbidity study conducted in 2007-2008 [3]. Specific objectives include the following:

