### Data Analysis

The patterns of morbidity in primary care will be presented by descriptive statistics for the prevalence of health problems and diseases, as well as the rates of management activities (referral, investigation, prescription, preventive care), weighted for the proportion of private and public primary care doctors in Hong Kong. The pattern of morbidity will be compared with the previous pattern in 2007-2008. All estimates will be accompanied by 95% CIs.

Stratified estimates in the patterns of morbidity in primary care by public and private doctors will also be reported and compared with the previous pattern in 2007-2008. The influence of the health care sector on morbidity patterns will be assessed by comparing the prevalence and rates of public and private doctors by nonlinear mixed effects analysis with logit link that accounts for potential covariance among health problems from the same doctor.

Factors associated with morbidity and management patterns in primary care will be assessed by nonlinear mixed effects model with logit link to cater for the dichotomous outcomes. Potential factors including patient demographics (age, sex), doctor background characteristics (age, qualifications, years of practice, type of practice, average number of consultations, participation in primary care initiatives), and nature of problem (acute, chronic, preventive) will be taken as covariates in the model. Both univariable and multivariable analyses will be performed. In the multivariable analysis, the presence of multicollinearity will be assessed by examining the tolerance. Factors involved in multicollinearity will only be considered one at a time.

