On the other hand, practice-based morbidity surveys are a feasible option for capturing accurate and more comprehensive data [25]. They allow documentation of actual consultations, reflecting the patient’s reason for seeking care and the doctor’s diagnostic interpretation of the illness, which can be standardized by validated tools [16]. Both of these features are essential in health care service planning, which must rely on accurate information about health problems but also consider patient need. Because of this, such surveys continue to be used on a large scale in the United States, where the Centers for Disease Control and Prevention initiated the National Ambulatory Medical Care Survey in 1973 and has been running it annually since 1989 [26]. In Australia, the Bettering the Evaluation and Care of Health program collected general practitioner–patient encounter data for 18 years until 2016. These data were used widely for policy development and to improve Australian health care delivery and patient care [27]. Practice-based morbidity studies conducted in primary care settings have proven (and continue) to be a useful and reliable methodology for documenting disease prevalence and for service planning [6,10,28-32].

An issue that we encountered in the sample size calculation was whether we could assume that the number of health problems needed to encounter in each season should be evenly distributed. Such an assumption may not necessarily be reasonable, particularly for some season-specific diseases. However, based on the raw data of the earlier Hong Kong morbidity study, the overall most commonly occurring diagnosis was upper respiratory infection (26.4% of encounters), which was also the most commonly occurring diagnosis in all 4 seasons, ranging in frequency from 32.1% in winter to 22.7% in spring. The 14 diagnoses that account for >1% of visits were the same top 14 diagnoses across all 4 seasons and there was only variation in the order of frequency in each season. This is consistent with data from a study on the seasonal variation in diagnoses in primary care based on the United States National Ambulatory Medical Care Survey [33]. The key finding was that there was little seasonal variation among the 23 most commonly occurring diagnoses (which accounted for >1% of encounters)—only the rank order of the diagnoses varied from season to season.

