### Limitations

This study was originally planned and approved prior to the start of the COVID-19 pandemic. We delayed the implementation in the hope that the pandemic would pass quickly but as this has not happened, we will proceed with the expectation that the effect of COVID-19 will be a limitation of the study as it is affecting usual patient health care–seeking behaviors including for chronic disease [34]. We will also seize the opportunity to capture the full period of the worst (fifth) wave of the COVID-19 pandemic in Hong Kong and to examine how stringent pandemic control measures by the Hong Kong Government affect primary care consultations, and presumably the patterns after the surge has eased and things have returned back to normal.

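### The main aim, change since 2007-08, is compared with no stated adjustment for season, age or sex, although the 18-month calendar counts spring and summer twice

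*Protocol article*

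**What the plan says.** The Introduction states the aim: "This study aims to determine the changes in morbidity and management patterns in Hong Kong primary care", measured against the 2007-08 survey. The Abstract's objective also includes this comparison.

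Data Analysis deals with it in two places. The overall estimates are "weighted for the proportion of private and public primary care doctors in Hong Kong", and then "The pattern of morbidity will be compared with the previous pattern in 2007-2008". Next, "Stratified estimates in the patterns of morbidity in primary care by public and private doctors will also be reported and compared with the previous pattern" of the earlier survey. All estimates are to carry 95% confidence intervals. Both comparison sentences name morbidity only, although the aim also covers management.

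The same section specifies mixed models with a logit link for two other questions: public versus private sector, and factors associated with morbidity and management. The factor model takes patient age and sex as covariates. Survey period is a term in neither model.

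Four other statements bear on the point:
- Confounding Variables lists patient demographics.
- The Introduction reports that between 2005 and 2015 "there has been an increase in the proportion of people aged 65 years or older", and says that trends would give an indication of the impact of government primary care initiatives.
- Data Collection sets one week a month for 18 months from March 2021, with three-month seasons.
- The Discussion (Overview) gives seasonal frequencies "based on the raw data of the earlier Hong Kong morbidity study".

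**The concern.** The question the study exists to answer has the least specified analysis, while models are written out for the other objectives. Two features of the design can create a difference between the surveys when nothing has changed within a season or an age group.

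The first is the calendar. Eighteen months starting in March contain two springs and two summers but only one autumn and one winter. The earlier survey is described as covering one year. Any diagnosis that varies by season will therefore shift when the new data are pooled over all weeks.

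The second is age mix. The article itself reports an older population, so a diagnosis whose frequency depends on age will change its share of all problems.

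At stake is how the headline result is interpreted. A shift produced by the calendar is an artefact under any reading. A shift produced by ageing is a real change in workload, but it is not evidence of a change in age-specific morbidity or of the effect of an initiative. The pandemic adds a third influence, since the study also intends to "capture the full period of the worst (fifth) wave of the COVID-19 pandemic in Hong Kong".

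**Working it through.** **1. The plan's own precision figure.** Sample Size Calculation: p = 0.5, error d = 0.005, 95% confidence.
n = z² p(1−p)/d² = 1.95996² × 0.25 / 0.000025 = 38,414.6, rounded up to 38,415. This reproduces. It is the size for one proportion in one survey, not for a difference between surveys. The 0.5-point error is used below as the yardstick.

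**2. Season weights.** Data Collection: 18 monthly weeks, March 2021 to August 2022; spring March-May, summer June-August, autumn September-November, winter December-February.
- Spring: 3 + 3 = 6 weeks
- Summer: 3 + 3 = 6 weeks
- Autumn: 3 weeks
- Winter: 3 weeks

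The weights are 1/3, 1/3, 1/6 and 1/6. A doctor who gives one week per season for six seasons has the same mix (2, 2, 1, 1).

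**3. Seasonal rates.** Discussion (Overview), upper respiratory infection in 2007-08: 26.4% overall, 32.1% in winter (highest), 22.7% in spring (lowest). Summer (S) and autumn (A) are not given. Assuming equal volume per season in 2007-08:
S + A = 4 × 26.4 − 32.1 − 22.7 = 50.8, a mean of 25.4.

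**4. The 2007-08 rates under the new calendar,** with equal volume per week:
(22.7 + S)/3 + (A + 32.1)/6
- S = A = 25.4: 48.1/3 + 57.5/6 = 16.03 + 9.58 = 25.6, a fall of 0.8 points.
- S = 22.7, A = 28.1 (summer as low as spring): 45.4/3 + 60.2/6 = 15.13 + 10.03 = 25.2, a fall of 1.2 points.
- S = 28.1, A = 22.7 (autumn as low as spring): 50.8/3 + 54.8/6 = 16.93 + 9.13 = 26.1, a fall of 0.3 points.

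With the four seasons weighted equally instead, (22.7 + 50.8 + 32.1)/4 = 26.4, so the artefact is zero whatever S is.

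**5. Ageing (all inputs assumed; the article gives no age mix or age-specific rates).** Spurious change = rise in the 65+ share × difference in age-specific proportions. If the share of problems from patients aged 65+ rises from 15% to 20%, and a diagnosis makes up 40% of problems in that group and 20% in younger patients: 0.05 × (40 − 20) = 1.0 point, with no age-specific change. With assumed rises of 4 to 10 points:
- smallest: 0.04 × (30 − 15) = 0.6 points
- largest: 0.10 × (60 − 20) = 4.0 points

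**6. Interval for a change (assumed inputs).** Take p = 26.4%, 109 doctors with 69,973 problems in 2007-08, and assume 40 doctors with 40,000 problems now.
Half-width = 1.96 × √{p(1−p)[D₀/69,973 + D₁/40,000]}, where D = 1 + (m − 1) × ICC and m (problems per doctor) = 642 and 1,000.
- ICC 0: 0.54 points
- ICC 0.01: 1.69 points
- ICC 0.05: 3.61 points

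The method used for the interval therefore matters. The article states doctor correlation only for the sector model.

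**The case against.** The strongest reply is that this is a condensed article. It says the patterns will be compared; it does not say the comparison ignores age, sex, season or doctor. The listed confounders are not tied to one objective, and the detailed method may sit in a fuller plan. That carries weight as far as missing detail goes. It does not dispose of the point, because the article does set out its models and the main aim falls outside them, and because the published calendar has a built-in imbalance that sector weighting and sector stratification do not remove.

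A second reply stands in full. The unstandardised change is a legitimate measure of presenting workload, and the Introduction names ageing among the changes whose impact it wants to document. That estimate should stay. The COVID-19 effect is also already declared as a limitation.

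Four stronger readings are tempting and are not supported:
- A reader might infer that the comparison is crude and ignores sector mix. It does not: estimates are sector-weighted and also compared within sector. What is unstated is whether the 2007-08 figures receive the same weights.
- A reader might infer that the intervals ignore doctors, and so calculate an inflated false-positive rate. The article names no test and no interval method for this comparison, so no such rate can be assigned.
- A reader might infer that ageing will be reported as a change in morbidity. That is conjecture; the article says only that trends would give an indication of the initiatives' impact.
- A reader might infer that a pooled record-level analysis is certainly possible. The raw 2007-08 data were used for diagnosis by season. Nothing shows that the file holds patient age, sex or doctor identifiers.

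**Conclusion.** The point holds in this form: the change since 2007-08 has no stated adjustment for season, age or sex and no survey-period term in any model, and the calendar by itself distorts a pooled comparison. For upper respiratory infection the artefact is a fall of about 0.8 points (0.3 to 1.2), larger than the 0.5-point target error in the central case but not at the lower end of the range. This rests on equal volume per season in 2007-08 and equal volume per week now, and on holding the 2007-08 seasonal rates fixed to isolate the calendar effect.

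The ageing shift of 0.6 to 4.0 points is an illustration on assumed figures and shows only that the effect can be of similar or greater size. With doctor clustering, the interval for a change may be wider than the seasonal artefact. That does not excuse the artefact, which is systematic and does not shrink with more data.

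This should be corrected in the analysis. It does not invalidate the data collection.

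**What to change.** In Data Analysis, replace the comparison sentence with a short specification:

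1. Keep the sector-weighted, otherwise unadjusted change since 2007-08 as the description of workload. Weight the four seasons equally, or compare season by season, and apply the same sector weights to both surveys.
2. Add a change standardised for age, sex and season. If the 2007-08 file holds age, sex and doctor identifiers, a pooled mixed logit model could serve instead, with survey, sector, age, sex, season and a doctor random intercept.
3. Apply this to management outcomes as well as morbidity.
4. State that confidence intervals for the change allow for clustering by doctor.
5. Report the change with and without the fifth-wave months, naming those months in advance because the article does not date them.
6. State that the change will not be attributed to the government initiatives.

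Cost: extra analysis work and no new data collection, since age and sex are already on the encounter form. The age-sex part depends on what the 2007-08 file contains. If it lacks those items, the season correction still looks feasible, because diagnosis by season has already been tabulated from that file.

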### Sample Size Calculation

The sample size calculation is based on the first two primary objectives of our study, which are to determine the proportion of health problems/diagnoses among all clinical encounters and the proportion of various management activities in terms of prescription, investigation, referral, and preventive care. The 2007-2008 morbidity study found that respiratory conditions comprised the largest proportion of problems (36.2%) and among these, upper respiratory tract infection was the most common diagnosis (26.4%) [10]. On this basis, if we conservatively anticipate the proportion of a type of health problem/diagnosis to be 50% with a confidence interval of 95% and a maximum error of 0.5%, we will need to encounter at least 38,415 health problems over one year. This translates to about 10,000 health problems per season. In the 2007-2008 morbidity study, 109 doctors recorded 69,973 health problems over the course of the year, which meant that on average, each doctor encountered about 250 health problems in one week. Based on this estimation, 40 doctor-weeks will be required to encounter the requisite number of health problems for each season. Assuming there is a one-third dropout rate of doctors, 60 doctor-weeks per season will be required. According to a general population study on service utilization patterns in primary care, around 80% of those who visit a Western medical practitioner would attend a private clinic whereas the remaining 20% would attend publicly funded primary care services [12]. Considering this, we need 48 doctors from the private sector and 12 doctors from the public sector to participate in the study.

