### Recruitment of Subjects

Because there is no complete, publicly available primary care doctor register with contact information, we will undertake a targeted recruitment. We will recruit doctors in the Primary Care Research Network established during a previous study on the epidemiology of depression in primary care conducted by the Department of Family Medicine and Primary Care at The University of Hong Kong. This resulted in a network of 60 primary care doctors across 45 practices who expressed interest to participate in future research studies [14]. In addition, we will invite members of the Hong Kong College of Family Physicians, honorary teachers of the Department of Family Medicine and Primary Care at The University of Hong Kong and the Division of Family Medicine, School of Public Health at the Chinese University of Hong Kong. We will also specifically target doctors listed in the Primary Care Directory, a voluntary directory, and the doctors listed as service providers in the GOPC Public-Private Partnership Programme on the corresponding websites. Those who are interested will receive a briefing on the study by the principal investigator and/or a member of the research team and provide written informed consent if they wish to participate.

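### The headline prevalences and rates are sized as independent observations and have no stated allowance for clustering by doctor, although the plan recognises that clustering in its sector comparison

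*Protocol article*

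**What the plan says.** In the protocol article, Data Analysis presents prevalences and management rates as descriptive statistics, weighted by the public and private shares of doctors and set against the 2007-2008 survey. Sector-stratified versions will also be reported. On uncertainty it says "All estimates will be accompanied by 95% CIs" and names no variance method. Within-doctor covariance appears once, for the sector comparison, which uses "nonlinear mixed effects analysis with logit link that accounts for potential covariance among health problems from the same doctor". The analysis of associated factors is also a mixed effects logit model, but its grouping level is not named.

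Sample Size Calculation rests on the prevalence and management-rate objectives. It anticipates a proportion of "50% with a confidence interval of 95% and a maximum error of 0.5" percent and concludes that "we will need to encounter at least 38,415 health problems over one year". It then converts problems to doctors on the basis that "each doctor encountered about 250 health problems in one week", which leads to "40 doctor-weeks will be required to encounter the requisite number of health problems for each season" and, after dropout, "Assuming there is a one-third dropout rate of doctors, 60 doctor-weeks per season will be required". Data Collection plans six weeks per doctor.

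Recruitment of Subjects describes one source as "a network of 60 primary care doctors across 45 practices".

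**The concern.** Problems recorded by one doctor share that doctor's patient mix, coding habits, prescribing and referral style. The plan accepts this when it compares sectors. For the estimates that the study is sized on, the only variance the article shows is the independent binomial one.

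Clusters are large here, so even a small ICC matters. If the planning variance were carried into the analysis, the CIs on the headline figures would be materially too narrow. The comparison with 2007-2008 is the stated aim, and it would suffer most, because ordinary differences between two sets of doctors could be read as change over time. The Introduction treats a one-point rise on a 2.5% referral rate as important for services, so the size of the error bars bears on the study's own use of the results.

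**Working it through.** **Inputs from the protocol article.** p = 0.50, maximum error d = 0.005, 95% confidence, about 250 problems per doctor-week, 40 doctor-weeks per season rising to 60 with one-third dropout (Sample Size Calculation); six weeks per doctor (Data Collection); 60 doctors in 45 practices (Recruitment of Subjects).

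**Input not in the article.** The ICC. Assumed 0.005 to 0.01.

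**Step 1: reproduce the plan's figure.** n = z²p(1−p)/d² = 1.96² × 0.25 / 0.005² = 38,414.6 (z unrounded), so 38,415, an exact match. The rest of the chain also follows: 38,415/4 = 9,604, stated as about 10,000; 10,000/250 = 40; 40/(1 − 1/3) = 60. No step contains a design effect.

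**Step 2: problems per doctor.** One week gives m = 250. Six weeks give m = 6 × 250 = 1,500.

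**Step 3: design effect.** D = 1 + (m − 1) × ICC. The true half-width is 0.50 × √D points at n = 38,415. A nominal 95% binomial CI covers 2Φ(1.96/√D) − 1.

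| m | Assumed ICC | D | √D | Half-width (points) | Coverage of a binomial CI |
|---|---|---|---|---|---|
| 250 | 0.005 | 2.245 | 1.50 | 0.75 | 81% |
| 250 | 0.01 | 3.49 | 1.87 | 0.93 | 71% |
| 1,500 | 0.005 | 8.495 | 2.91 | 1.46 | 50% |
| 1,500 | 0.01 | 15.99 | 4.00 | 2.00 | 38% |

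For the most common earlier diagnosis (26.4%), the half-width rises from 0.44 points to between 0.66 and 1.76. For a 2.5% rate on the same n, it rises from 0.16 to between 0.23 and 0.62. A larger ICC makes this worse: at 0.05 and m = 1,500, D = 75.95 and the half-width at p = 50% is 4.36 points.

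**Step 4: does collecting six weeks rescue the precision?** The table holds n at 38,415. If 40 doctors each complete six weeks, n = 40 × 1,500 = 60,000. The independent half-width is then 1.96 × √(0.25/60,000) = 0.40 points. Multiplied by 2.91 and 4.00, it becomes about 1.17 and 1.60 points, still well above 0.5. The coverage column does not change, because it depends on D alone.

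**Step 5: shared practices.** The network averages 60/45 = 1.33 doctors per practice. If doctor-level effects within a practice correlate at an assumed 0.1 to 0.5, the standard error rises by √(1 + 0.33 × 0.1) = 1.02 to √(1 + 0.33 × 0.5) = 1.08, that is by 2% to 8%. With an assumed four doctors per clinic, the factors are √1.3 = 1.14 and √2.5 = 1.58.

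**Limits.** Clusters are taken as equal in size and the weighting is ignored. The 250 per week is the plan's own figure and cannot be verified: 69,973/109 = 642 problems per doctor over the earlier survey, which matches 250 a week only at about 2.6 weeks per doctor, and the article does not give the number of weeks.

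**The case against.** A journal article condenses a fuller protocol, and a variance method for CIs is commonly left to the analysis plan. The article does not say that the CIs will be binomial, and its authors plainly know about within-doctor covariance. A reader might infer that the headline CIs will ignore clustering. That is not stated, and the sample size formula is direct evidence about planning precision only. This part of the objection stands, so the coverage figures above are conditional.

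A reader might also infer that clustering is handled in the sector comparison alone. That is too strong, because the analysis of associated factors is a mixed effects model too, with its grouping level unnamed.

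A third tempting reading is that both models need a practice random intercept. The article does not support this. The 60 doctors in 45 practices are one recruitment source among several, solo practices are eligible, and at that ratio the effect on the standard error is 2% to 8%. With 12 public doctors planned, a further variance component could also be poorly estimated.

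What the objection does not remove is the inconsistency within the article. A maximum error of 0.5% is stated as the study's precision, it holds only with a design effect of 1, and the analysis section gives the reason to doubt that value.

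**Conclusion.** The point holds in a limited form. The 0.5-point precision is attained only under independence. At assumed ICCs of 0.005 to 0.01 and 250 to 1,500 problems per doctor, the half-width at p = 50% is about 0.75 to 2.0 points. CIs computed on the planning variance would be about 1.5 to 4 times too narrow, with coverage of about 81% down to 38%. The first statement follows from the plan's own formula. The sizes rest on the assumed ICCs, and the coverage figures also rest on the planning variance being used in the analysis, which the article neither states nor rules out. The practice level is secondary: small at the one documented ratio, and potentially larger only if several public doctors share a clinic.

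**What to change.** - State that the weighted prevalences, management rates, sector-stratified estimates and 2007-2008 contrasts will have 95% CIs with doctor as the cluster and sector as the stratum. Use Taylor linearisation or a cluster bootstrap, with t-based inference on the number of doctors. The t reference matters most for the public stratum: 12 doctors planned, or 12 × 2/3 = 8 after the assumed loss.
- Apply the same variance to the earlier survey in the comparison. The Discussion shows that its raw data are available to the team.
- In Sample Size Calculation, say that the 0.5% maximum error assumes independence, or restate it over a range of ICCs as in the table above.
- Record a practice identifier on the background form. Where participating doctors share a site, repeat the CIs with practice as the cluster, as a sensitivity check.

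The cost is wording, one identifier and a routine survey procedure, with no additional patients or doctor-weeks. The intervals will be wider and the stated precision less favourable.
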